#### Data quality

Assessors will be trained to competence on the interview outcome measures (CAPS-5 and PSYRATs scales) [67, 69] prior to starting any assessments, i.e. they will need to have reached > 80% agreement with ratings made by the Trial Coordinators on training videos during the initial training stage. Agreement will be based on symptom presence ratings for the CAPS 5 (i.e. scores of 2 or above for each item of criteria B-E) and individual item scores for the PSYRATS. Once started, assessments will be recorded, with participants’ consent, to conduct further inter-rater reliability on the interview measures. Each research worker’s assessments will be double-rated by the Trial Coordinator until > 80% agreement has been reached. These procedures will be repeated every 4–6 months to minimise rater drift. Inter-rater reliability for our primary outcome will be reported from the double ratings made throughout the lifetime of the trial for a minimum of 60 ratings (excluding those used for rating agreement during the initial competency training stage prior to obtaining > 80% agreement).

#### Measures

All measures were selected or designed with the participant population in mind and are considered suitable for people with psychosis to complete. A range of potential measures for each domain of assessment was presented to our experts-by-experience advisory group who made the final selection, based on consideration of content acceptability and burden. An extra questionnaire will be administered to capture contextual information relating to the Covid-19 pandemic such as the degree of restrictions at the time of assessment, level of lockdown in the previous month, and how much Covid-19 has impacted on the person.

##### Primary outcome

PTSD symptom severity in the past month will be assessed on the CAPS-5 [69]. The CAPS-5 is a semi-structured interview assessing the severity of symptoms delineated in DSM-5 [35].

The CAPS-5 consists of seven criteria (Criteria A to G). Scores are anchored to an index event, which will be elicited using the mini-TALE and TALE checklists [61, 62]. The index event could be a single trauma experience or multiple incidents. In this study, meeting Criterion A (i.e. only events including objective actual or threatened death, serious injury, or sexual violence) will not be a requirement, as we will include events related to psychosis and its consequences (e.g. hearing a threatening voice, involuntary admission or forced restraint), emotional and physical neglect, discrimination, and attachment disrupting experiences, as possible index events [68]. PTSD diagnostic status will be determined by an algorithm of minimum scores on specific items from Criteria B to E, and meeting Criteria F and G, according to DSM-5 diagnostic rules.

Once the index event has been ascertained, the severity of symptoms is scored on a 5-point scale (‘absent’ to ‘extreme’) on four criteria: (i) Criterion B: Re-experiencing symptoms; (ii) Criterion C: Avoidance symptoms; (iii) Criterion D: Cognitions and mood symptoms; (iv) Criterion E: Arousal and reactivity symptoms. Criteria F and G are scored dichotomously (Yes/No) on whether the duration of the experience is more than 1 m, and has caused subjective distress and impairment in functioning, respectively. The total symptom severity score (total of 20 item scores on Criteria B to E) will be the primary outcome.

##### Secondary outcomes

All measures listed below consist of standardised questionnaires and semi-structured interviews, with demonstrated reliability and validity. Short forms have been included when available, to minimise participant burden. The timescale of assessment will be the past month for all symptom measures, consistent with our primary outcome (apart from substance use, which will be 3 months as the timescale cannot be amended, and the economic measures). All have been used in previous trials with psychosis populations and were endorsed by our experts-by-experience advisory groups.

#### Symptoms

##### PTSD

PTSD includes the following: (i) percentage of people who achieve a loss of their PTSD diagnosis, as determined by the CAPS-5 diagnostic status algorithm; (ii) percentage of people who show a clinically significant improvement and a reliable change in CAPS-5 scores; (iii) CAPS-5 individual symptom clusters (severity scores for the individual Criteria B to E); (iv) self-reported PTSD symptoms and their associated appraisals and responses will be assessed on standardised, commonly used questionnaires: International Trauma Questionnaire (ITQ [75]); PTSD and DSO dimensional scales (6 items each); Brief Version of the Posttraumatic Cognitions Inventory (PTCI-9 [76]; 9 items), which measures cognitive appraisals of the trauma and its aftermath; Dissociative Subtype of PTSD Scale (DSPS; 15 items [77];), which assesses lifetime occurrence and current frequency and intensity of dissociative symptoms (consisting of three factors of dissociation, namely psychogenic amnesia, derealisation/depersonalisation, and loss of awareness).

##### Psychosis

(i) The Psychosis Symptoms Rating Scales (PSYRATS [67]) is a clinician-administered semi-structured interview and will be used to assess the multidimensional aspects of delusions and auditory hallucinations (such as distress, preoccupation, and conviction; 11 items for voices, and six items for delusions). The PSYRATS is well suited to assess outcome in psychological therapies [78] and has been used in major RCTs [63, 64]. PSYRATS items will also be administered for hallucinations in other modalities (i.e. non-verbal auditory; visual; somatic; sexual sensations; olfactory; gustatory; sense of presence [79]), and additional items will be included at the baseline assessment to assess multi-modality (i.e. whether different types of hallucinations are experienced simultaneously or serially and are related or unrelated) [80].

Each PSYRATS item is rated by the interviewer on a 5-point nominal scale (0–4). An additional, continuous self-report rating scale will be added to each item, as there is evidence that the nominal scale is not sensitive to change for some of the items (e.g. delusional conviction is rated as a 3 for conviction ratings of 50–99%, and as 4 for 100%; therefore, a 50% change in delusional conviction only incurs a 1-point difference). The rating scale will be presented in the form of a thermometer to facilitate self-report. Both ratings (total scores for each PSYRATS scale) will be reported as secondary outcomes.

(ii) Self-reported paranoia (the commonest form of delusions) will be assessed using the Revised Green et al Paranoid Thoughts Scale (GPTS-R [81];; 18 items).

##### Emotional well-being

(i) Mood will be assessed using the short form of the Depression Anxiety Stress Scales (DASS-21 [82]), which includes seven items for each of the three domains assessed. (ii) Suicidal ideation will be assessed using the Paykel Suicidal Feelings Scale (PSFS [83]; 5 items). (iii) Substance use will be assessed by the Brief Version of the Alcohol, Smoking and Substance Involvement Screening Test (ASSIST [84, 85];) developed by the World Health Organization (WHO). It comprises 10 items pertaining to lifetime (Part 1) and recent (Part 2) use of substances.

##### Psychological recovery

Psychological recovery will be assessed using the Short Version (11 items + 1 personal goal) of the CHOICE (CHoice of Outcome In Cbt for psychosEs) scale [86]. CHOICE was developed by our group in collaboration with experts-by-experience, reflecting themes they considered important psychological therapy outcomes.

##### Social and occupational functioning

This will be assessed using the Personal and Social Performance Scale (PSP [87]). It is a 100-point single-item rating scale based on the assessment of functioning in four areas (socially useful activities, personal and social relationships, self-care, and disturbing and aggressive behaviour). For an impairment to be rated, it must relate to psychological problems rather than lack of opportunity.

##### COVID-19 context questionnaire

Contextual information will be captured using a 7-item scale assessing mode of assessment and current level of pandemic restrictions; personal lockdown circumstances; and impact of the pandemic on day-to-day life, well-being, and PTSD and psychosis symptoms.

#### Economic measures

##### Health-related quality of life

Health-related quality of life will be measured using the 5-level version of the EuroQol 5-dimensions (EQ-5D-5L [88]), introduced by the EuroQol Group as an alternative to the standard EQ-5D-3 L, to provide greater sensitivity and to reduce ceiling effects. The EQ-5D-5L descriptive system comprises five dimensions (mobility, self-care, usual activities, pain/discomfort, and anxiety/depression) each with five levels (no problems, slight problems, moderate problems, severe problems, and extreme problems). Participants are asked to respond on the basis of which answer best describes their health ‘today’. The score for each dimension can be combined into a 5-digit number that describes the person’s health state.

##### Health-related quality of life for users of mental health services

We will additionally include the Recovering Quality of Life (ReQoL-10 items [89]), which may be more sensitive to change than the EQ-5D in populations with severe mental health problems [90]. Respondents are required to answer on a 5-point scale assessing their thoughts, feelings, activities, and physical health over the last week.

##### Service use

Service use for costing purposes will be measured in interview using a modified version of the Adult Service Use Schedule (AD-SUS), designed, and successfully applied in psychosis populations [91]. The STAR AD-SUS will measure use of all-cause health and social services appropriate for the NICE preferred NHS/Personal Social Services perspective [92].

#### Therapy group only

##### Acceptability

A qualitative interview will be designed to explore participant acceptability and satisfaction with the therapy. Close attention will be paid to any emotional distress resulting from memory reprocessing procedures, in particular potential impact on psychotic symptoms, and whether this was considered unacceptable or unnecessary. The views of those who chose to end therapy early will be gathered at point of ending, using additional questions about their reasons for doing so and to identify barriers and potential solutions to engagement in therapy. Therapists will be interviewed once they have completed therapy with a minimum of two participants to obtain feedback about acceptability, and any potential difficulties in delivery.

Experts by experience researchers with lived experience of psychosis will conduct the participant interviews, with appropriate supervision and support, and therapists will be interviewed by research workers. It is anticipated that the final patient sample will be representative and include variance on key variables (e.g. therapy engagement, age, gender, ethnicity, clinical presentation). All interview data will be recorded, with participants’ permission, and transcribed verbatim for analysis.

##### Therapeutic alliance

We will assess the therapeutic alliance between therapists and participants in the therapy group to monitor the potential impact of different modes of therapy delivery, implemented as a result of the Covid-19 pandemic, on the therapeutic relationships. The therapists and client versions of the Working Alliance Inventory – Short Form Revised (WAI-SR) [93] will be used. Three key aspects of alliance are assessed: agreement on therapy tasks, agreement on therapy goals, and the development of an affective bond [93]. Both the self-report participant and therapist versions will be completed at three time points (sessions 3, 13, and last session). The therapists will be blind to participant ratings at all time points.

### Plans to promote participant retention and complete follow-up {18b}

A number of strategies are planned to maximise participant retention into the trial and ensure completeness of outcomes. A ± 1 m window will be allowed for completion of assessments at each time point. Assessment measures will be clearly prioritised so that the most important will be collected first to avoid missing data. The CAPS-5 [69] (primary outcome) will always be administered first, followed by the PSYRATS [67] and the health economy measures.

Participants who choose to end the therapy early or deviate from the allocation protocol (e.g. someone receiving trauma-focused therapy in the TAU group) will still be invited to complete all follow-up assessments. Participants will be remunerated for their time and travel, which secures good concordance with trial procedures, even in those who end therapy early [94]. There will be flexibility around the location of assessments, including remote assessments or home visits for participants who are unable to travel. Anyone who moves within the UK will be followed up.

A mid-therapy assessment is included to minimise attrition from the trial, as 9 m is a long period without contact with the research team for this population. This is particularly the case for the control group and those who end therapy early, and the extra assessment stage will provide data that can be used in the linear mixed model for the intention-to-treat analysis for those who drop out of the study at the primary endpoint. This adds some validation to a missing-at-random assumption for outcome missingness. The four ‘keeping in touch’ phone calls will also help to retain participants in the trial until the final assessment 24 m post-randomisation.

### Data management {19}

All data are anonymised at source. No patient identifiable information is recorded on the research assessment records, and the computerised database is held centrally and managed by the King’s Clinical Trials Unit (KCTU). A web-based electronic data capture (EDC) system will be designed, using the InferMed Macro 4 system. The EDC will be created in collaboration with the trial analyst/s and the Trial Coordinator and maintained by the KCTU for the duration of the project. It will be hosted on a dedicated server within KCL.

Source data will be entered by the research workers at each site by authorised staff onto the EDC. A full audit trial of data entry and any subsequent changes to entered data will be automatically date and time stamped, alongside information about the user making the entry/changes within the system. Database access will be strictly restricted through user-specific passwords to the authorised research team members. The data management plan is in the study site file and can be provided on request.

Data quality will be ensured by close monitoring and routine auditing for accuracy throughout the data collection period. To ensure the accuracy of the data entered into the database, the main outcome measure entry will be checked for 20% of participants by comparing the paper record with that on the database. An error rate of no more than 5% is acceptable. If the error rate is higher than 5%, the percentage of participants checked will increase to a minimum 50%. No data will be amended independently of the study site responsible for entering the data. Prior to analysis of the 9 m and 24 m outcomes, there will be a central process of data cleaning and checking to verify that all data are complete and correct. At this point, data can be formally locked for analysis of that timepoint.

Pseudonymised recordings of the qualitative interviews will be transcribed by a KCL-approved transcription service. All recordings will be transferred and stored securely, and the transcription service will follow GDPR regulations (2018).

### Confidentiality {27}

#### Clinical confidentiality

Issues relating to confidentiality will be addressed at the eligibility stage and potential participants will be advised of the limits of confidentiality. It is also possible that disclosure of criminal or other acts potentially requiring action will occur during assessment and therapy sessions. The research team will be trained in both local and national policies for dealing with such disclosures and will follow our Standard Operational Procedures for managing risk disclosures. Therapists will address confidentiality issues again with participants allocated to the TF-CBTp group at the start of therapy, and at any appropriate subsequent points during the therapy.

#### Data confidentiality

Research data will be confidential unless a participant discloses information that indicates that they or another person are at risk of harm. If harm is disclosed, the research worker or trial therapist would be required to share this information with the participant’s care team and documented in the NHS trust’s electronic patient record system.

All research data will be pseudonymised. A hard copy of a record sheet linking Participant Identifiable Data (PID) (participant identity, contact details, trial identification number) for all participants will be kept separate from the research data at each site. The participant record sheet, and details necessary for communication with clinical teams, will be placed securely in locked filling cabinets separate from research datasheets. During the COVID-19 pandemic, staff may have to work remotely outside of Trust premises; an electronic version of the record sheet linking PID will be created and saved on secure Trust drives accessible online.

All data will be kept secure at all times and maintained in accordance with General Data Protection Regulation (GDPR, 2018) requirements and archived according to clinical trial Good Clinical Practice regulations. Participant consent forms will be retained, kept confidential, and stored securely. All identifiable data will be destroyed following a period of 10 years (as determined by relevant information governance policies) after the completion of the trial.

No participant identifiable information is recorded on the research assessment records and the computerised database is held centrally and managed by the KCTU. Data from the assessments are entered into this central record by research workers using a secure network connection.

Therapy files will be kept in a secure office and are not accessible to the staff collecting the research outcome data.

#### Recordings

Encrypted recording equipment (such as encrypted smart phone, laptop, or equivalent devices) will be used to record assessments (with participant consent) to check fidelity to assessment protocols and allow for multiple ratings of assessments to ensure inter-rater reliability. The therapy sessions will also be recorded (with participant consent) for monitoring the fidelity of the intervention delivery. These files named with a unique participant identifier will be transferred to secure central storage as soon as possible and stored as computer files on secure NHS/ University servers. Recordings of the therapy will be accessible to the participant’s therapist, the supervisor, and a random selection to the independent fidelity rater. With additional, optional participant consent, anonymised therapy excerpts will be used for training and dissemination purposes.

The study will adhere to the joint guidance on secure recording issued by KCL and the NHS Trusts. When not in use, encrypted devices will be stored in a locked cabinet within a locked office. Each device will be password protected. In the event of the device being lost or stolen, this will be reported as a data incident to the Information Management and Compliance Team at KCL and the Information Governance Team at the relevant NHS Trust. Any sensitive data on a lost/stolen device will be remotely erased.

Pseudonymised audio recordings of the qualitative interviews will be transcribed by a KCL-approved transcription service. All recordings will be transferred and stored securely, and the transcription service will follow GDPR regulations (2018).

### Plans for collection, laboratory evaluation, and storage of biological specimens for genetic or molecular analysis in this trial/future use {33}

N/A

## Statistical methods

### Statistical methods for primary and secondary outcomes {20a}

#### Primary and secondary outcomes

We will report data in line with the CONSORT-SPI [74] statement showing attrition rates and loss to follow-up. All analyses will be carried out using the intention to treat principle, incorporating data from all participants including those who do not complete therapy. Every effort will be made to follow up all participants in both arms for research assessments.

Analyses will be conducted in Stata version 15 or later. Descriptive statistics within each randomised group will be presented for baseline values. These will include counts and percentages for binary and categorical variables, and means and standard deviations, or medians with lower and upper quartiles, for continuous variables, along with minimum and maximum values and counts of missing values. There will be no tests of statistical significance or confidence intervals for differences between randomised groups on any baseline variable.

Treatment effects on primary and secondary outcomes will be estimated using linear mixed models. Fixed effects will be centre, baseline assessment for the outcome under investigation, group, time (categorical), and time × group interactions. Participant and therapist will be included as random intercepts. Marginal treatment effects will be estimated and reported for each time point as adjusted mean differences in scores between the groups with 95% confidence intervals and 2-sided *p*-values. For binary secondary outcomes, the same approach will be followed using logistic mixed models and effects will be reported as conditional odds ratios.

The analysis will be conducted in two separate stages. The primary analysis will estimate treatment effects at the primary endpoint of 9 m, using all outcome data from 4 and 9 months. Analysis will take place after the last participant has completed their 9 m assessment and will report the estimated effects at 4 and 9 months. The results will not be shared with the blinded assessors, nor outside of the STAR team, until all 24-m assessments have been completed, to avoid any biases on data collection.

The secondary analysis will estimate treatment effects at 24 m, using all outcomes from 4, 9, and 24 months. Analysis will take place after the last participant has completed their 24-m assessment, and will report the estimated effect at 24 m.

Cohen’s *D* [21] effect sizes will be calculated as the adjusted mean difference of the outcome divided by the pooled sample standard deviation of the outcome at baseline. These will be displayed in a forest plot showing the therapy effects on the primary and the secondary outcomes at 9 and 24 months post-randomisation.

Missing data on individual measures will be pro-rated if more than 80–90% (depending on questionnaire) of the items are completed; otherwise, the measure will be considered as missing. We will check for differential predictors of missing outcomes by comparing responders to non-responders on key baseline variables. Any significant predictors will be included in the analysis models. This accounts for missing outcome data under a missing at random assumption, conditional on the covariates included in the model. As a sensitivity analysis, we will assess whether therapy adherence is associated with missing data and, if it is associated, use inverse probability weights or multiple imputation to compare results.

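### Significance tests of missingness add covariates to the pre-named primary model and decide whether the IPW/MI sensitivity analysis runs; at the planned attrition these tests are weak gates

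*Protocol article*

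**What the plan says.** All the main statements are in the protocol article's section on statistical methods for primary and secondary outcomes {20a}.

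- Core model: "Fixed effects will be centre, baseline assessment for the outcome under investigation, group, time (categorical), and time × group interactions". Also: "Participant and therapist will be included as random intercepts".
- Screening: "We will check for differential predictors of missing outcomes by comparing responders to non-responders on key baseline variables". The article lists neither the variables nor a significance level.
- Selection rule: "Any significant predictors will be included in the analysis models".
- Assumption claimed as a result: "This accounts for missing outcome data under a missing at random assumption, conditional on the covariates included in the model".
- Sensitivity analysis: "we will assess whether therapy adherence is associated with missing data and, if it is associated, use inverse probability weights or multiple imputation".

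The section on non-adherence and missing data {20c} repeats maximum likelihood under missing at random (MAR). It adds that weighting may also be used, with adherence and intermediate outcomes as predictors of later loss. The retention section {18b} says of the 4-month assessment: "This adds some validation to a missing-at-random assumption for outcome missingness".

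**The concern.** The first group of statements fixes a model and the selection rule reopens it. The covariates for 9-month CAPS-5 are not known until missingness has been observed. They may differ from one outcome to the next, and between the 9-month and 24-month stages, because the pattern of loss will differ. A statistical analysis plan (SAP) can supply the candidate list and the threshold, but while it follows this rule it cannot fix the model. The economic analysis section also asks for covariates that are pre-specified and consistent with the clinical analyses, which is hard to meet if the clinical set depends on later tests.

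Significance is also the wrong criterion. A covariate helps against bias from missing outcomes if it relates both to missingness and to the outcome. The planned test looks only at the first relation, and its result depends on how many people happen to be missing. A real predictor can be passed over, and a variable unrelated to CAPS-5 can enter.

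The same difficulty affects the sensitivity analysis. Adherence, as defined in section {11c}, is sessions offered and attended, so it exists only in the TF-CBTp arm. The test that decides whether the analysis runs therefore uses half the sample. At stake is the missing-data protection of the primary result in a trial that plans for 20% loss and in which participants know their allocation.

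**Working it through.** **Inputs from the sample size section {14}:** 300 randomised, 150 per group; 20% attrition; 120 per group analysed; effect size 0.4; SD after baseline adjustment 0.866; ICC 0.01; 10 therapists with a mean of 12 participants and cluster-size variation of 12; level 0.05; stated power 91%.

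**Step 1. Reproduce the plan's figure.** Read the variation of 12 as a variance, so CV² = 12/144.
- Design effect in the therapy arm = 1 + ((1 + 12/144) × 12 − 1) × 0.01 = 1.12.
- SE = 0.866 × √(1.12/120 + 1/120) = 0.115.
- Non-central t with Satterthwaite df of about 30.4: power 92.0%, against 91% stated. The other two stated figures give 85.2% (stated 85%) and 79.3% (stated 80%).

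The planned numbers are coherent, so they can be used below. Missing = 0.20 × 300 = 60, observed = 240. In the therapy arm, if loss is equal by arm, missing = 0.20 × 150 = 30, observed = 120.

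**Step 2. Chance that the baseline screen flags a real difference.** Assumption: two-sided 0.05, since no threshold is given. Non-centrality = d / √(1/60 + 1/240) = d / 0.1443.

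| d (SD) | Non-centrality | Flagged (normal) | Flagged (t) |
|---|---|---|---|
| 0.2 | 1.39 | 28% | 28% |
| 0.3 | 2.08 | 55% | 54% |
| 0.4 | 2.77 | 79% | 79% |

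**Step 3. Chance that the adherence test triggers the sensitivity analysis.** Same assumption, therapy arm only. Non-centrality = d / √(1/30 + 1/120) = d / 0.2041.

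| d (SD) | Non-centrality | Triggered (normal) | Triggered (t) |
|---|---|---|---|
| 0.3 | 1.47 | 31% | 31% |
| 0.4 | 1.96 | 50% | 49% |

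**Step 4. Chance that at least one irrelevant variable enters.** The number of candidates is not stated, so a range is shown, assuming independent tests: 1 − 0.95^k = 23% for k = 5, 40% for k = 10, 64% for k = 20.

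**Step 5. Does the rule distort the test of treatment?** An illustrative simulation used ANCOVA, 300 randomised, about 20% missing and 10 assumed candidates.

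| Setting | Selection rule | Fixed model |
|---|---|---|
| Type I error, no true predictor of missingness | 5.0% | 5.0% |
| Type I error, one true predictor | 4.9% | 4.6% |
| Power at effect 0.4, one true predictor | 95.3% | 94.9% |

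Bias was about 0.002 SD or less throughout. The simulation omits the 4-month outcome and therapist clustering, and missingness depended on the covariate in the same way in both arms. It shows no inflation in this setting. It does not show that the rule protects against arm-specific loss.

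**The case against.** The strongest reply is that little is at risk. The core terms, including baseline CAPS-5, are named in advance, and the 4-month outcome contributes through the repeated-measures model. Only additions are data-driven. The rule is itself stated beforehand and uses baseline data and missingness, not the estimated treatment effect. A null covariate that enters by chance costs about one degree of freedom, and Step 5 finds no inflation. All of this stands, and it limits the point to an undetermined model and a weak gate.

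It is also fair that section {20c} allows weighting without the adherence trigger, so the triggered analysis is not the only one mentioned. But that weighting is optional; the analysis the protocol commits to is the conditional one.

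Three stronger readings are tempting and not supported:

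- A reader might infer that the primary model as a whole is chosen by significance tests. The listed fixed and random effects rule this out.
- A reader might infer that no analysis departing from MAR is planned, so that the key assumption goes untested. The methods named here for the clinical outcomes (maximum likelihood, weighting, imputation) are ordinarily MAR methods, but a delta-adjusted analysis may be in the SAP, which is not shown. MAR also cannot be tested from observed data. For that reason the 4-month data can make it more plausible but not validate it, and the retention section's own claim is the modest one of adding some support.
- A reader might attach a large bias to the rule. If unobserved therapy-arm outcomes alone were 0.25 to 0.5 SD worse than MAR predicts, the effect would move by 0.20 × 0.25 = 0.05 to 0.20 × 0.5 = 0.10 SD, or 12.5% to 25% of 0.4. That shift comes entirely from the assumed one-arm departure, not from the selection rule. With equal loss and the same departure in both arms the effect is unchanged.

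**Conclusion.** The point holds in limited form. The protocol states two gates, and an SAP that follows it would keep both. At planned attrition the baseline gate detects differences of 0.2 to 0.4 SD with probability 28% to 79%. The adherence gate detects 0.3 to 0.4 SD with probability 31% to 49%, so at these differences the committed sensitivity analysis would be skipped at least about half the time. Neither gate considers the relation to CAPS-5.

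The harm is a primary model not settled before the data and a missing-data check that depends on the power of a small test. It is not a demonstrated bias or an excess of false positives. The figures assume a 0.05 threshold, 20% attrition split equally between arms, and comparison of approximately normal variables. Heavier or lighter loss would change them. This should be changed, but it does not undermine the design.

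**What to change.** Replace the sentence "Any significant predictors will be included in the analysis models" with a primary model limited to the stated fixed and random effects plus any covariates named in advance for their expected relation to both CAPS-5 and missingness.

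Remove the condition in "if it is associated, use inverse probability weights or multiple imputation to compare results". Choose one method beforehand and always run it, whatever the association test shows. If it is multiple imputation, impute separately by arm with a pre-named auxiliary set, including sessions attended in the TF-CBTp arm. Separate imputation is needed because sessions attended has no counterpart under TAU. The comparison of responders with non-responders can stay as a description.

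Also check whether the SAP contains an arm-specific delta-adjusted analysis of 9-month CAPS-5, and consider adding one if it does not. This is a recommendation to confirm, not an established omission.

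The cost is some rewording and a little more analysis work, with no change to trial conduct. The downside is that a predictor of missingness nobody anticipated will not enter the primary model and can be used only in the sensitivity analysis.
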